# Sphenopalatine ganglion stimulation with one acupuncture needle for moderate-severe persistent allergic rhinitis: study protocol for a multicenter randomized controlled trial

**DOI:** 10.1186/s13063-015-0707-0

**Published:** 2015-04-23

**Keywords:** Study protocol, Randomized controlled trial, Sphenopalatine ganglion, Persistent allergic rhinitis, Acupuncture, Traditional Chinese medicine

## Abstract

**Background:**

Allergic rhinitis is a symptomatic allergic disease of the nose that affects 10 to 20% of the global population. Chinese otolaryngologists use one acupuncture needle to stimulate the sphenopalatine ganglion because of its potential advantages for treating moderate-severe persistent allergic rhinitis compared with traditional Chinese acupuncture (verum acupuncture); however, little evidence is available to support the wide clinical use thus far. Therefore, we propose a protocol for a parallel, multicenter, assessor-blinded, randomized controlled trial to evaluate sphenopalatine ganglion stimulation with one acupuncture needle compared to verum acupuncture for treatment of moderate-severe persistent allergic rhinitis.

**Methods:**

In the trial, 96 patients previously diagnosed with moderate-severe persistent allergic rhinitis and meeting all inclusion criteria will be allocated to one of two equal therapeutic groups by using a computer-generated randomization list. The interventional group will receive sphenopalatine ganglion stimulation with one acupuncture needle for 4 weeks (once or twice weekly, total four to eight sessions); attending physicians will decide whether the second session is required in a week by examining signs and symptoms. The control group will receive individualized verum acupuncture for 4 weeks (twice weekly, total eight sessions). Follow-up evaluations will be performed 1 month later. The primary outcome measure is the change in the total nasal symptom score from the baseline to week 4. The secondary outcome measures include onset time and duration of effectiveness in every session, change in number of days with moderate-severe persistent allergic rhinitis from the baseline to week 8, change in total immunoglobulin E level and eosinophil count in venous blood from the baseline to week 4, change in Rhinoconjunctivitis Quality of Life Questionnaire score from the baseline to week 4, and clinical waiting time.

**Discussion:**

The trial should provide evidence for the benefits of sphenopalatine ganglion stimulation with one acupuncture needle for treating moderate-severe persistent allergic rhinitis, including better change in total nasal symptom score, faster onset time, longer duration of effectiveness, and shorter treatment time.

**Trial registration:**

Current Controlled Trials: ISRCTN21980724 (registered on 27 March 2014).

**Electronic supplementary material:**

The online version of this article (doi:10.1186/s13063-015-0707-0) contains supplementary material, which is available to authorized users.

## Background

Allergic rhinitis is a symptomatic disorder of the nose induced by immunoglobulin E (IgE)-mediated inflammation of the nasal membranes after allergen exposure [1] and can be classified into intermittent and persistent allergic rhinitis (PER). It has a reported prevalence of approximately 10 to 20% globally and 11.1% in China [2]. Allergic rhinitis causes major illness and disability worldwide and reduces the quality of life and productivity regardless of ethnicity, gender, and age [3]. Some patients develop asthma, further increasing medical and social burdens.

Conventional medical treatments for PER include H1-antihistamines, glucocorticosteroids, leukotriene antagonists, decongestants, anticholinergics, and specific immunotherapy [4]. However, several patients experience side effects, become dissatisfied, and seek complementary and alternative treatments [5,6]. In traditional Chinese medicine, physicians have effectively used verum acupuncture to treat allergic rhinitis for many years [7,8]. Interestingly, a large case study suggested that sphenopalatine ganglion stimulation with one acupuncture needle, a technique developed by a Chinese otolaryngologist and applied in more than 130,000 Chinese patients [9], offers potential advantages with regard to nasal symptoms, onset time, duration of effectiveness, and quality of life.

A recent pilot nonrandomized study (ten patients per group) revealed significantly improved total nasal symptom score (TNSS [10]) (*P* <0.05), total non-nasal symptom score (TNNSS [11]) (*P* <0.05), and Rhinoconjunctivitis Quality of Life Questionnaire (RQLQ [12,13]) score (*P* <0.001) after sphenopalatine ganglion stimulation with one acupuncture needle than after verum acupuncture. After each session, the onset time of effectiveness was shorter (*P* <0.001) and duration of effectiveness was longer (*P* <0.001). Further, patients had fewer symptomatic days one month after sphenopalatine ganglion stimulation (*P* <0.001). On the basis of these results, we propose a protocol for a parallel multicenter assessor-blinded randomized controlled trial to evaluate sphenopalatine ganglion stimulation with one acupuncture needle compared to verum acupuncture for treatment of moderate-severe PER.

## Methods

### Ethics

The study design and methodology adhere to the principles of the Declaration of Helsinki and have been approved by the Xiyuan Hospital Ethics Committee (December 31, 2013; approval number 2013XL062-2). The trial is registered in the ISRCTN register (Current Controlled Trials) as ISRCTN21980724. Each participant will receive an explanation regarding the study protocol and written consent will be obtained. All participants will receive documentation regarding the study protocol and are free to withdraw at any time.

### Study setting

The study will be simultaneously conducted at Xiyuan Hospital, Beijing Tongren Hospital, Beijing Baiwan Chinese Medical Clinic, and Beijing Dacheng Acupuncture Hospital, Beijing, China. It will run from January 2014 to October 2015.

### Sample size

We used the symptomatic outcome of the pilot study (10:10 cases in each group) to calculate the sample size in PASS 2008 software (NCSS, Kaysville, UT). The means for the score of TNSS, serially assessed during the 4-week treatment period, was 4.2071 ± 2.58702 after sphenopalatine ganglion stimulation and 7.4393 ± 2.0368 after verum acupuncture. For a power of 0.9 to detect a significant difference (α = 0.01, two sided), 15 participants per group are required. Forty cases will be enrolled in consideration of four centers’ research capabilities. Allowing for a 20% dropout rate, 48 participants will be enrolled in each group, yielding 96 patients for the study.

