Our pilot study revealed that sphenopalatine ganglion stimulation with one acupuncture needle yields significant differences in onset time, duration of effectiveness, TNSS, RQLQ score, and number of post-treatment symptomatic days compared with verum acupuncture. Experts in allergic rhinitis were consulted to decide which endpoints to adopt for sample size calculation. They concluded that changes in TNSS are generally applied, and this scoring system has been validated [18]. Therefore, the mean TNSS was used to calculate the sample size for the trial. Furthermore, the research group consensually decided that TNSS should replace onset time and duration of effectiveness, reported in the ISRCTN registry, as the primary outcome measure of the trial. Only 15 cases per group, total 30, are needed based on the sample calculation. As the small sample size may be increase the risk of bias, we decided to increase the patient number to 40 in each group in consideration of each center’s research capabilities. Allowing a drop-out rate of 20%, 96 participants will be enrolled in the study. All other endpoints are considered as secondary outcome measures. The total IgE level and eosinophil count in venous blood will be measured to investigate the mechanism underlying the effect of acupuncture.

We will measure the clinical waiting time to investigate economic benefits. Sphenopalatine ganglion stimulation with an acupuncture needle requires only approximately 1.5 min and no bed. In contrast, patients spend an average of 2 h to receive acupuncture in Chinese hospitals, including 1.5 h or longer waiting for a bed and 20 min or longer per session.

The proposed trial has several methodological limitations. The acupuncturists and participants cannot be blinded because of the difference in acupuncture techniques and control required while needling. However, the acupuncturists will be trained to not communicate the therapeutic procedures and responses to the participants and outcome assessors. Furthermore, this study will not allow us to determine whether the observed efficacy is caused by placebo effects, intensity of provider contact, or physiological effects of needling. The bias resulting from the lack of blinding cannot be totally excluded. Finally, the sample size is small.

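### The 20% dropout allowance was added to 40 per group instead of being taken from those enrolled: 48 per group leaves about 38 completers, or 40 only if dropout is at most 16.7%

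*Protocol article*

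**What the plan says.** The Sample size section of the protocol article bases its calculation on pilot TNSS values of "4.2071 ± 2.58702 after sphenopalatine ganglion stimulation" and "7.4393 ± 2.0368 after verum acupuncture". The criterion is "For a power of 0.9 to detect a significant difference (α = 0.01, two sided", and the result is that "15 participants per group are required". It then moves to forty cases on grounds of what the four centers can manage, and closes: "Allowing for a 20% dropout rate, 48 participants will be enrolled in each group, yielding 96 patients for the study".

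The Discussion gives the same sequence and makes clear that forty is a per-group number: "we decided to increase the patient number to 40 in each group in consideration of each center’s research capabilities". The total follows: "Allowing a drop-out rate of 20%, 96 participants will be enrolled in the study".

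The chain in both places is therefore 15, then 40, then 48 per group, or 96 in all. Neither place says what the 20% is a percentage of, and neither gives a different number to be retained.

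**The concern.** An allowance for dropout only has meaning if the smaller number, 40 per group, is what should remain after the losses. The enrolled number must then be large enough that 80% of it is 40, and 48 is not. Target, dropout rate and enrolment do not fit together on the ordinary meaning of a dropout rate.

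What is at stake is the accuracy of the sample size statement. Readers will judge the finished trial against it. If dropout runs exactly as planned, the trial will report about 38 completers per group and will seem to have missed a target of 40, although everything went as foreseen. The Discussion also offers 40 per group as its response to the worry about a small sample, so the figure should be one that the plan delivers on its own assumptions.

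**Working it through.** **Inputs**
- Calculated requirement: 15 per group (Sample size; Discussion).
- Raised target: 40 per group (Discussion; the Sample size section gives forty without naming the group).
- Dropout: 20% (both sections).
- Enrolment: 48 per group, 96 in total (Sample size); 96 in total (Discussion).
- Pilot TNSS: means 4.2071 and 7.4393, SDs 2.58702 and 2.0368 (Sample size).

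**1. Reproduce the plan's figure.** Target × (1 + rate) = 40 × 1.20 = 48 per group; 2 × 48 = 96. This matches exactly, so the origin of the figure is clear.

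**2. What 48 leaves.** Enrolled × (1 − rate) = 48 × 0.80 = 38.4 per group. In total, 96 × 0.80 = 76.8, against 80 for 40 per group.

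**3. What would keep 40.** Target / (1 − rate) = 40 / 0.80 = 50 per group, 100 in total. That is 2 more per group and 4 more overall than planned.

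**4. Dropout that 48 does cover.** 1 − 40/48 = 8/48 = 16.7% of those enrolled. The eight extra patients are 20% only of the 40 who remain (8/40).

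**5. Which analysis set is affected.** The Statistical analysis section defines the per-protocol set as those who completed the study, so the 38.4 applies there. The intention-to-treat set keeps anyone with at least one measurable outcome after treatment, with the last observation carried forward, and Table 2 schedules TNSS in each of weeks 1 to 4. At 20% dropout there are 48 × 0.20 = 9.6 dropouts per group. The intention-to-treat set then lies between 38.4 (no dropout has a post-treatment value) and 48 (all have one). It reaches 40 if 1.6 of the 9.6, one in six, have such a value.

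**6. Effect on power.** Difference = 7.4393 − 4.2071 = 3.2322. Pooled SD = √[(2.58702² + 2.0368²)/2] = 2.328. At two-sided 1% and 90% power, the normal approximation gives 2 × (2.328/3.2322)² × (2.576 + 1.282)² ≈ 15.4, so 16 per group (the plan has 15). The t-test gives 18. At 38 and 40 per group:

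| | 38 per group | 40 per group |
|---|---|---|
| Power for 3.2322, two-sided 1% (t-test) | 0.9996 | 0.9998 |
| Difference detectable with 90% power, two-sided 5% | 1.75 | 1.71 |
| Difference detectable with 90% power, two-sided 1% | 2.11 | 2.05 |

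The detectable difference grows by 0.04 to 0.06 TNSS points, against a planning difference of 3.23.

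**The case against.** The strongest reply is that nothing inferential depends on 40. The calculation asks for 15 per group, and 40 was chosen for what the centers can handle. Falling 1.6 short of it breaches no stated power, significance level or effect size, and 38 is more than twice even the 18 that a t-test calculation gives. This stands in full, and it sets the severity.

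Second, the article never calls 40 an evaluable number; the Sample size section speaks of enrolling forty cases. That is correct as to wording. But if 40 were not the number meant to remain, the section would give two conflicting enrolment figures in consecutive sentences. The Discussion's order (increase to 40, then allow for dropout) supports the ordinary reading.

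Third, the figures agree if 20% is read as a share of the 40 who remain. The denominator is not defined, so this cannot be ruled out as the intention. It is not what a dropout rate usually means, however, and a reader would need to be told.

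Fourth, dropouts with a post-treatment measurement stay in the intention-to-treat analysis. This also stands: the shortfall belongs to the completers, and the intention-to-treat set may well hold 40 or more.

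A reader might infer from the slip that the trial is underpowered, or that it must recruit 100 patients. The documents support neither. Power on the plan's own inputs is practically the same at 38 and 40, and 40 was not derived from a power requirement.

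**Conclusion.** The sample size statement is wrong as written, and the correction is minor. Multiplying by 1.20 instead of dividing by 0.80 makes 48 per group look sufficient for 40 after 20% dropout. It leaves about 38 completers per group, or it covers dropout of at most 16.7%. The gap is under two completers per group, 76.8 against 80 overall.

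This rests on two readings: that the dropout rate is a share of those enrolled, and that 40 is the number meant to remain. Both are the natural reading, though neither is spelled out. The power comparison also assumes that the pilot means and SDs hold in the trial.

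It would go too far to say that the plan fails to deliver 40 analysable patients per group in every analysis. That depends on when dropouts leave, and concerns chiefly the per-protocol set.

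**What to change.** Keep enrolment at 96 and reword the allowance in both the Sample size section and the Discussion, using one of these:

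- 48 per group will be enrolled; with 20% dropout, about 38 per group are expected to complete the study.
- 48 per group will be enrolled, which allows for dropout of about 17% of those enrolled while keeping 40 per group.

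The first keeps the dropout rate and gives up 40 as the number of completers; the second keeps 40 and lowers the rate. Either is acceptable, provided both sections say the same.

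The cost is one sentence in two places, with no extra patients and no change to the design or analysis. Going to 50 per group would also remove the inconsistency but is not needed. A detectable difference for 38 per group could be added, but the plan states none for 40, so that would be new content and is not part of the correction.

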### Recruitment

Patients will be recruited from the outpatient clinics of the four participating hospitals. Posters describing the required population, free blood and allergic testing of eligible patients, and contact information of the researcher will also be displayed in the clinics. Moreover, television advertisements will be used to publicize the recruitment.

### Baseline assessment

During the run-in period (baseline), the physical sign score (measured at least twice), TNSS and TNNSS (measured once daily), RQLQ score (measured at least once), and total IgE level and eosinophil count in venous blood will be determined.

### Inclusion criteria

To be eligible, participants should be previously diagnosed with moderate-severe PER, according to the Allergic Rhinitis and Its Impact on Asthma (ARIA) criteria, and meet the following requirements:Have had PER for more than 4 days/week, and more than 4 consecutive weeks, with a disease course of more than 1 year.Age range from 18 to 60 years.Completed AR baseline questionnaire and provided written informed consent.Physical sign score ≥1 and symptom score ≥4.

### Exclusion criteria

Patients will be excluded if they meet the following criteria:Acute sinusitis, active asthma, or diagnosis or suspicion of pneumonia.Nasal abnormalities or rhinopolypus (polypoid lesions can be included).Consumed antihistamines, anticholinergics, corticosteroids, decongestants or antibiotics within 2 weeks before enrollment.Received systemically administered corticosteroids within 6 months or special immune therapy within 1 year before enrollment.Received an alternative and complementary modality, that is, acupuncture or herbal medication, for treatment of AR within 2 months before enrollment.Pregnancy or planning for pregnancy.Serious medical conditions such as uncontrolled hypertension, diabetes mellitus requiring insulin injection, past or current malignant tumor, severe dyslipidemia or liver and kidney dysfunction, anemia, active pulmonary tuberculosis, other infectious diseases, or systemic diseases that cannot be treated by acupuncture.Heavy smoker.

### Randomization and blinding

This is a multicenter prospective, randomized controlled clinical trial. The central randomization will be executed by the Xiyuan Hospital, which will use block randomization to generate the random allocation sequence and prepare predetermined computer-made randomization opaque sealed envelopes. The envelopes will be numbered consecutively and connected into a strain. Each envelope will be separated from the strain and then opened in sequence only after the run-in period when the participants are registered in the trial. Outcome assessors and personnel who deal with the data collection and data analysis will be blinded throughout the entire trial. The acupuncturist and patients cannot be blinded because of the nature of the two different acupuncture techniques in this trial, but the physicians are trained not to communicate with the participants or outcome assessors regarding the treatment procedures and responses. To ensure that all practices at each of the four hospitals are the same, physicians who will enroll participants and assessors who will collect data in the four hospitals will be asked to have a 3-day training seminar concerning treatment modalities and trial documentation prior to the trial. Periodic check-ups on the practices will be performed in each hospital.

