### Procedure

Based on the predetermined randomization envelopes, participants will be randomly allocated to the intervention group or control group (Figure 1). The patients will have an equal probability of being assigned to either of the two groups. Participants will be asked to record symptoms in a rhinitis diary from the run-in period to the 4th week after randomization, and the usage of acute symptomatic relief medication will be recorded during the treatment period. The case report form contains all of the outcome measures and the rhinitis diary will be collected separately from the four hospitals in the 4th week after randomization by blinded interviewers. Blinded telephone interviewers will contact the participants regarding the days of moderate to severe allergic rhinitis during the 4 weeks after the treatment period to evaluate the long-term effect of acupuncture in the 8th week after randomization.

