### Statistical analysis

Data will be analyzed by the following principles: (i) intention-to-treat analysis (participants who have at least one measurable outcome after treatment; missing data will be replaced according to the principle of last observation carried forward) and (ii) and per-protocol analysis (participants who have completed the study). A variance analysis will be performed to reject the global hypothesis that “There is no difference in all fields of means between the groups.” The significance level is 5%; therefore *P* <0.05 indicates a significance difference.

The means of TNSS and TNNSS will be compared by analysis of variance (ANOVA) for repeated measures between the groups. Mean onset time and duration of effectiveness will be compared by *t*-test between the groups. Analysis of variance (ANOVA) for repeated measures will be used for between-group comparisons of RQLQ scores. The other continuous variables (total IgE level and eosinophil count in venous blood, number of symptomatic days, and clinical waiting time) will be compared by *t*-test. Comparisons within groups will be performed by multivariate ANOVA followed by Tukey’s post hoc test. Stratified analysis within the four hospitals will be performed to control for confounding factors, if necessary. The incidence of adverse events will be calculated and compared between the groups by using the chi-squared test or Fisher’s exact test. All analyses will be performed in SPSS version 13.0 (SPSS, Chicago, IL).

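### Hospital stratification is not stated for the allocation, and hospital adjustment in the analysis is left to an undefined condition; hospital should be a prespecified factor

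*Protocol article*

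**What the plan says.** Allocation (protocol article, Randomization and blinding): randomization is central. One hospital "will use block randomization to generate the random allocation sequence" and also makes up the concealed envelopes. On their form the article says: "The envelopes will be numbered consecutively and connected into a strain". They are used in order, one for each participant, once the run-in is over and the participant has been entered in the trial. Neither block size nor any stratification factor is named. The Procedure section adds 1:1 allocation: "The patients will have an equal probability of being assigned to either of the two groups".

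Sites (Study setting): "The study will be simultaneously conducted at Xiyuan Hospital" and three other Beijing institutions.

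Analysis (Statistical analysis): "The means of TNSS and TNNSS will be compared by analysis of variance (ANOVA) for repeated measures between the groups". The quality-of-life score is also compared by repeated-measures ANOVA, and the other continuous outcomes by t-test. None of these comparisons is given a hospital term. Hospital appears once: "Stratified analysis within the four hospitals will be performed to control for confounding factors, if necessary".

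**The concern.** Blocks drawn from one list that several hospitals use in turn balance the arms overall but not within any hospital. A blocked list per hospital would limit the imbalance in each hospital to part of a block. The article does not say which arrangement applies, and its analysis section does not make up for that: the named comparisons are unadjusted, and no criterion says when the hospital-stratified analysis becomes necessary.

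Two things are at stake. The first is precision: under a shared list, any difference between hospitals in outcome level enters the unadjusted arm difference as extra chance variation. The second is pre-specification: without a stated criterion, the choice between an unadjusted and a hospital-stratified result can be made after both are seen. Hospital is a plausible source of variation here. The Interventions section makes the technique depend on operator experience, and the Discussion describes waiting for a bed as the main part of an acupuncture visit. The allocation section itself requires training and periodic checks to keep practice the same across the four hospitals.

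**Working it through.** **Inputs from the article.** 96 patients, 48 per arm, four hospitals. Pilot TNSS values: "was 4.2071 ± 2.58702 after sphenopalatine ganglion stimulation and 7.4393 ± 2.0368 after verum acupuncture". The difference is 7.4393 − 4.2071 = 3.2322, and the pooled SD is √[(2.58702² + 2.0368²)/2] = √5.4206 = 2.328.

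**Assumptions, none of them in the article.** Four hospitals of 24 patients arriving in random order; blocks of 4 or 8; between-hospital SD s of 0.5, 1.0 or 1.5 TNSS points.

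**Plan's own figure.** The normal approximation at two-sided α = 0.01 and power 0.9 gives n = 2 × [2.328 × (2.576 + 1.282)/3.2322]² = 15.4 per group. The stated figure is 15, which is close enough to confirm that these are the plan's inputs. This point disputes no stated number.

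**Step 1: imbalance in one hospital under a shared list.** The number in one arm among a hospital's 24 patients is approximately hypergeometric (24 drawn from 96, 48 per arm). Its variance is 24 × ½ × ½ × (72/95) = 4.547. The probability of a 15:9 split or worse, in either direction, is 0.238.

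**Step 2: at least one of four hospitals.** If hospitals were independent this would be 1 − (1 − 0.238)⁴ = 0.66. They are not independent, because the overall totals are fixed. Simulation with permuted blocks of 4 or 8 (40,000 replicates) gives 0.59 for 15:9 or worse and 0.30 for 16:8 or worse. A separate simulation with blocks of 4, 6 or 8 gives 0.58 to 0.61 for equal hospitals and 0.51 to 0.53 for sizes 48/24/12/12, for an arm difference of 6 or more. With one blocked list per hospital, a difference of 6 or more never occurred.

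**Step 3: effect on the arm difference.** The hospital contribution is Σ b_h × d_h/48, where d_h is the arm difference in hospital h and b_h is its effect, with SD s. Its expectation is zero. Since E(d_h²) = 4 × 4.547 = 18.19, its variance is s² × 4 × 18.19/48² = 0.0316 s², an SD of 0.178 s. The sampling variance without hospital effects is 5.4206 × 2/48 = 0.2259, a standard error of 0.475.

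| Assumed s | SD of contribution | Added variance | 95th percentile of absolute shift |
|---|---|---|---|
| 0.5 | 0.089 | 0.0079/0.2259 = 3.5% | 0.18 |
| 1.0 | 0.178 | 0.0316/0.2259 = 14% | 0.37 |
| 1.5 | 0.267 | 0.0711/0.2259 = 31% | 0.55 |

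The second simulation gives an SD of 0.20 to 0.21 per unit of between-hospital SD. It scales the SD to the four realised hospitals instead of a wider population of hospitals; for equal sizes, 0.178/√(3/4) = 0.205, so the two agree. With a blocked list per hospital the figure is 0 to 0.07.

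**Step 4: power.** At 40 per arm, for s from 0.5 to 1.5, the standard error rises from 0.52 to between 0.53 and 0.62. Power for a difference of 3.23 at α = 0.01 stays above 0.99.

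**Step 5: price of adjusting.** Under a shared list, if hospitals do not differ, fitting hospital costs on average 3/95 = 3.2% of the information on the arm difference. Simulation gives a mean relative efficiency of 0.968.

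**The case against.** A reader might infer that one envelope string is definitely shared by all four hospitals. The article does not say so. The support is singular grammar in a condensed text whose full protocol is not shown. A physical string of envelopes detached in order at four sites fits a string or segment per site at least as well, because a shared string would need a dispatch step that is not described. Block sizes and stratification factors are also details that an article may leave to the full protocol. This objection stands, and the shared list is treated here only as a possibility.

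A reader might also take the reserve stratified analysis as proof that hospital was not controlled by design. It is not: analysis by centre is just as usual after stratified allocation, and dropout can unbalance hospitals later.

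Third, under a shared list the expected bias is zero, and the shifts are small beside the planned 3.23 points. That stands too. Two limits apply: 3.23 comes from a nonrandomized pilot with ten patients per group, and if the true effect is smaller, a shift of 0.37 against a standard error of 0.475 is no longer negligible.

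Fourth, lists per hospital cannot separate operator from arm if different acupuncturists deliver the two arms within a hospital. The waiting-time contrast (about 1.5 minutes against an average of 2 hours) is too large for chance imbalance to alter. Both are correct, so neither is counted as a gain from this fix.

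None of these objections supplies the missing rule for when hospital enters the analysis.

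**Conclusion.** The point holds in a limited form. The article names no stratification by hospital, gives unadjusted group comparisons, and makes hospital adjustment depend on an unstated criterion. The last two hold whichever way the envelopes were organised. With a shared list, adjustment removes chance imbalance between hospitals; with lists per hospital, it makes the analysis match the design.

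The loss is one of precision and pre-specification. If the list is shared and hospitals are equal in size, a 15:9 split or worse somewhere is more likely than not (about 59%), and the added variance is about 3% to 31% over the assumed range of between-hospital SDs. The stronger conclusion, that hospital differences systematically distort the treatment comparison, is not supported: the imbalance is random, and power for the planned difference is hardly affected. The change is worth making because it is cheap and takes away a data-dependent choice, not because the primary result is in danger.

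**What to change.** **Statistical analysis section.** Replace the conditional sentence with a fixed rule: hospital is a prespecified factor in the repeated-measures model for TNSS and in the other between-group comparisons. Those now planned as t-tests become linear models with arm and hospital. This also serves patients already enrolled.

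**Randomization and blinding section.** State whether allocation is blocked within hospital. If it is not, use a separate 1:1 list and numbered envelope series per hospital for patients still to be randomized, with varying block sizes withheld from recruiting physicians, and record the date of the change. The Trial status section says that recruitment is open, so this is still possible.

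**Cost.** A short amendment and four lists instead of one, with no extra patients. The model uses 3 degrees of freedom, and about 3% of precision is lost if hospitals do not differ. Lists per hospital make the next arm slightly easier to guess within a site, which matters because acupuncturists are unblinded and which varying block sizes limit. They also allow up to half a block of imbalance per hospital. A change during recruitment leaves two allocation phases to report.
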